# Improving outcomes for primary school children at risk of cerebral visual impairment (the CVI project): protocol of a feasibility study for a cluster-randomised controlled trial and health economic evaluation

**DOI:** 10.1136/bmjopen-2020-044830

**Published:** 2021-05-05

**Keywords:** paediatric ophthalmology, developmental neurology & neurodisability, epidemiology

## Abstract

**Introduction:**

Cerebral visual impairment (CVI) refers to a spectrum of brain-related vision problems. CVI is associated with poor educational and mental health outcomes. An intervention has been developed to help children with CVI, involving input from clinicians, teachers and parents. The effectiveness of this intervention needs to be evaluated. This study aims to guide any refinements to the intervention or the design of a future cluster-randomised trial that may be needed.

**Methods and analysis:**

This study will include all methods anticipated for a future cluster-randomised controlled trial. Eight primary schools will be recruited and randomised to receive the intervention or carry on with usual practice. The intervention will comprise an information pack for schools and access to a local paediatric ophthalmology clinic (who are prepared to assess them for CVI), for up to 5% of participating children. Outcome assessments will be carried out at baseline (before randomisation) and after 4–5 months of intervention period. Assessments will include children’s self-reported quality of life, their learning ability and behaviour as reported by teachers, and family functioning reported by parents. Cost data will include service use, family expenditure on additional support (eg, private appointments and administration) and school spending and resource used in helping children with special educational needs or disability. A process evaluation (PE) will collect additional data relating to the implementation of the intervention and the trial processes, in the school and clinic settings. The protocol for the PE will be reported separately.

**Ethics and dissemination:**

Ethical permission was obtained from the University of Bristol Faculty of Health Sciences Ethical Committee. The results will inform the design of a future trial to assess the effectiveness and cost-effectiveness of the intervention and will be shared with participants, CVI-support groups and peer-viewed journals.

**Trial registration number:**

ISRCTN13762177; Pre-results.

Strengths and limitations of this studyAll elements/methods proposed for the future cluster-randomised controlled trial will be included, which will allow refinements to be made if needed.A detailed, mixed methods process evaluation is embedded.Children with cerebral visual impairment are not individually identified and the primary analysis will be instead a group presumed to be enriched with affected children, which will limit the statistical power.The duration of the study is limited to two terms so we cannot estimate long-term changes in implementation or effect.There is no provision to interview general practitioners to understand their views on the suggested referral pathway.

## Introduction

Damage or poor function in the brain areas related to vision leads to brain-related visual impairment, also known as cerebral visual impairment or impairments (CVI).^1^ There is not yet consensus on the specific type or severity of vision problems that should warrant a diagnosis of CVI, but there is general acceptance that brain-related vision disorders are important and a major cause of registrable blindness in the UK and other developed countries.^2^ A recent review suggested CVI was a verifiable visual impairment not attributable to ocular or optic nerve problems.^3^ Children with CVI may not be identified if they have good visual acuity;^4^ hence are not detected in visual screening programmes recommended for reception year (age 4–5 years) children.^5^ They are therefore at risk of poor outcomes because of lack of support.

Simple strategies can be helpful for children with CVI, including decluttering presentations, using a window to isolate part of the page, or using plain backgrounds.^6^ Decluttering can also increase engagement with lessons for children without known problems.^7^ However, there are no recommendations for teachers regarding CVI or vision problems in general and if these have been diagnosed, the child is usually referred to a specialist teacher (a qualified teacher for the visually impaired (QTVI)).

In a recent study by our group, at least 3.4% of all the children in primary schools we surveyed had CVI-related vision problems.^8^ We found that none of the potential indicators of higher risk for CVI-related vision problems (red flags) we examined were very accurate: having extra educational help was 79% sensitive but only 49% specific, while by contrast a vision-specific questionnaire was 91% specific but had only 13% sensitivity.

### Development of the complex intervention

We have developed a multilevel intervention that aims to improve outcomes for children with CVI. The intervention involves sharing information about the condition with the teachers, empowering them to try relevant strategies for children who are struggling and improving links between schools and the paediatric ophthalmology clinic.

Our previous study^8^ has suggested that on average at least one child per class has CVI-related vision problems and that the questionnaires we used do not accurately identify affected children in a community setting. The intervention therefore emphasises to teachers that universal approaches (eg, decluttering classrooms) will be helpful, as well as additional targeted approaches for children who are struggling. In this way, all children are exposed to potentially helpful ‘vision-friendly’ surroundings and there is less risk of a child getting no support because they are not yet diagnosed. A tiered approach using universal as well as targeted support has been recommended for other conditions affecting children, including anxiety and mental health problems.^9 10^

Families have told us that referrals to the eye clinic and treatment there can be difficult if there is little understanding of CVI. Another aspect of the intervention was therefore to provide an enhanced interface between the school and the eye clinic, by ensuring that the clinic was equipped and willing to accept referrals of children who may have CVI.

The school intervention pack materials were complied with advice from our professional advisory group (see below) and our local authority QTVIs and comprise the following:

A short (30 min) presentation with audio commentary by the study principal investigator (CW) giving an overview of CVI and how to help affected children and of the other materials provided, plus a transcript of the presentation.Links to existing online resources about CVI.A ‘Toolkit’—a word document detailing simple, inexpensive strategies (a) for universal use with whole class or school and (b) targeted measures to help individual children who are struggling with learning. These were reviewed and amended by our local QTVIs.Some teaching resources (stories and suggested activities for children to do), matched to the curriculum, for teachers to use to help explain topics related to vision and light.Guidance for teachers as to which children may have CVI and which may benefit from a referral to the eye clinic including suggested referral criteria.Letters for teachers to give to parents to show their general practitioners (GPs), requesting referral to the local paediatric ophthalmology clinic because vision problems are suspected. At the request of the University Faculty Ethical Committee, the number of study referrals was capped at 5% of participating children (to avoid overburdening the GPs or the eye clinic) although GPs can make whatever referrals they want outside of the study, in the usual way.

The eye clinic intervention materials comprise the following:

A validated questionnaire to score risk for CVI in at-risk children.^11^A protocol for vision tests to identify CVI-related vision problems, as used in our earlier study.^8^Sample advice sheets on how to help children with CVI, adapted from existing websites and resources^12 13^ augmented with input from our local QTVIs.A link to a secure Research Electronic Data Capture (REDCap, v9) database to enter the results of the vision tests and print out a summary report to give the families, schools and for the clinic notes.

As part of the process described by the Medical Research Council for the development of complex interventions,^14^ we need to evaluate this intervention and see if in real life, the intervention might need changing or adapting.

When and if we have evidence that the intervention is helpful, we will make the study materials including the advice sheets, available on request on our website (www.thecviproject.co.uk).

### How the intervention might work?

There are several pathways by which the intervention might potentially improve outcomes for children with CVI, for example, teachers adapting their teaching methods, or accurately identifying and referring affected children to the eye clinic. We have conceptualised these in a logic model and designed a process evaluation (PE) to collect data on what changes in school processes or attitudes if any, actually occur. We report the protocol for this separately (in press BMJ Open).

### Aim and objectives of this feasibility cluster-randomised controlled trial (cRCT)

The aim of this study is to assess the feasibility and acceptability of the new intervention and of the proposed trial methods, to inform the development of a future fully powered cluster-randomised controlled trial.

Our specific objectives are to collect data on the following:

Intervention-related outcomes as follows:

How the intervention is implemented in practice?—a detailed PE has been designed to do this as reported in a separate protocol paper (ref).Any changes in the outcome data (see table 1) that may indicate an effect of the intervention, to help us calculate the sample size needed for the future trial.Attitudes of teachers and parents to the intervention and whether it is beneficial.

**Table 1 T1:** Assessment tools to be used

Respondent	Concept being investigated	Tool	Format
Child	Quality of life	PedsQL Generic Core Scales: Child report: 8–12 years or child report: 5–7 years (supported by adult report)	Paper, in the classroom and supported by school staff Which form the child completes is at discretion of their teacher
Teacher	Child learning ability	PedsQL cognitive scales	Online REDCap form— one per child
	Child behaviour at school	SDQ with impact supplement	Online REDCap form—one per child
	Child behaviour that may indicate CVIs	5-item CVI questionnaire	Online REDCap form—one per child
	Teacher perception of their own teaching	Self-efficacy	Online REDCap form—one per teacher
Parents	Parental quality of life related to family	PedsQL family impact module	Paper Parents fill in one per child in the study
	Generic and child-related costs and resource input	Family expenses questionnaire (designed for the study)	Paper Parents fill in one per child in the study
	Child behaviour that may indicate CVIs	5-item CVI questionnaire	Paper Parents fill in one per child in the study

CVI, cerebral visual impairment; PedsQL, Pediatric Quality of Life Inventory TM; REDCap, Research Electronic Data Capture; SDQ, Strengths and Difficulties Questionnaire.

Study design-related outcomes as follows:

We will document the following:

The response rate and yield from recruitment flyers, letters and emails sent, any reasons given for non-participation and retention of schools once recruited (once they have signed the study paperwork—see below).The proportion and demographic predictors of parental non-agreement to data sharing in schools that have been recruited.The completeness of data from (a) child-report, (b) teacher-report and (c) parent questionnaires.The number of children suggested by the schools for a referral to the eye clinic, the proportion that attend the eye clinic and of those, the proportions who do and do not have any CVI-related vision problems.

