### Blinding and contamination

It will not be possible to blind school staff as to which arm of the study they are in, or the fieldwork staff, however analysis of the quantitative data will be carried out by a separate statistician who is blind to group allocation. The primary outcome for the definitive trial is planned to be the child’s self-reported QoL which should be subject to less allocation bias than the teacher-report would be. The feasibility of collecting the child-report data is therefore an important outcome from this study. The intervention group schools will be asked not to share the intervention materials; however, it is recognised that contamination between arms may occur and the PE will investigate this. If there is sharing of information by schools or by parents, we will note this and decide what changes should be made to the parent information leaflets provided in the future trial.

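### Unblinded teachers choose each child's PedsQL form and staff help with completion, so the planned primary outcome can be measured differently by arm at follow-up

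*Protocol article*

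**What the plan says.** Table 1 (under Aim and objectives) lists the child's quality of life as measured by the PedsQL Generic Core Scales in one of two versions: "Child report: 8–12 years or child report: 5–7 years (supported by adult report". The format is "Paper, in the classroom and supported by school staff", and the same cell adds "Which form the child completes is at discretion of their teacher". No age or reading criterion is given, and the article does not link the follow-up form to the baseline form.

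Blinding and contamination states: "It will not be possible to blind school staff as to which arm of the study they are in, or the fieldwork staff". The protection offered is that "analysis of the quantitative data will be carried out by a separate statistician who is blind to group allocation". The same section plans child-reported quality of life as the primary outcome of the definitive trial, on the ground that it is the "child’s self-reported QoL which should be subject to less allocation bias than the teacher-report would be". It also calls the feasibility of collecting child-report data an important outcome of this study.

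The Abstract places baseline before randomisation and follow-up after 4–5 months of intervention.

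**The concern.** Child report is preferred because the child's answers should be less affected by knowledge of the arm than a teacher's ratings. Table 1 nevertheless gives the teacher, who knows the arm at follow-up, a say in which instrument the child answers, and gives school staff a role in how it is answered. A blinded analyst cannot undo differences that arise while the data are being collected.

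The discretion probably falls most on the children of interest. The Introduction puts reception year at age 4–5, so Y3–Y5 are roughly 7 to 10. Most are old enough for the 8–12 form, and giving one of them the 5–7 form is largely a judgement about ability. The intervention pack tells teachers in one arm only how to recognise and help struggling children. A differential change in form or help is therefore plausible, in either direction.

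Three uses of the scores are exposed: the described change in quality of life, the sample size of the full trial, and the quality-adjusted life years obtained by mapping PedsQL to CHU9D. For a child who changes form, the change score also mixes a real change with a change of instrument. A larger trial would reduce random error but not this bias.

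**Working it through.** The article gives no figure for this point, so the check is a comparison of its statements followed by an illustration of scale.

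**Statements side by side**

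1. Form choice: the teacher's, without a stated criterion (Table 1).
2. Help: from school staff, in class (Table 1).
3. Knowledge of arm: school and fieldwork staff are unblinded (Blinding and contamination).
4. Timing: baseline precedes randomisation, so the baseline choice is safe. Only follow-up is exposed (Abstract).
5. Interval: Trial status puts baseline in December 2019–January 2020 and follow-up in January 2021. That crosses a school year, so a different teacher making a fresh choice is likely, though the article does not say so.

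**Size of a possible bias in extra-help children (assumed inputs)**

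Bias = (between-arm difference in the share changing form) × (mean score difference between forms).

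- Assumed switching difference 0.05 to 0.20; assumed form difference 5 points.
- 0.05 × 5 = 0.25 points; 0.20 × 5 = 1.0 point.

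**Diluted signal in the same group (assumed 5-point benefit in affected children only)**

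- Upper share, from Outcome assessment data: 42% of extra-help children had at least one CVI-related vision problem. 0.42 × 5 = 2.1 points.
- Lower share, from the Introduction (sensitivity 79%, specificity 49%, prevalence 3.4%): (0.79 × 0.034) / (0.79 × 0.034 + 0.51 × 0.966) = 0.0269 / 0.5195 = 0.052. 0.052 × 5 = about 0.26 points.
- The lower calculation implies that 52% of all children have extra help, so these figures and the 42% may not describe the same sample. They are used here only as the ends of a range.

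**Ratio of bias to signal**

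- At 42%: 0.25/2.1 = 12% to 1.0/2.1 = 48%.
- At about 5%: 0.25/0.26 = roughly equal, to 1.0/0.26 = nearly four times.

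**Random error, for scale (all children)**

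- The article's own sample-size sum reproduces: 1300 × 0.95 × 0.035 / 2 = 21.6, against its approximately 22.
- Children with data: 1300 × 0.95 / 2 = 617.5 per arm, and 1300 × 0.95 / 8 = 154.4 per school.
- With an assumed SD of 15, SE = 15 × √(2/617.5) × √(1 + 153.4 × ICC), which is 0.85 at ICC 0, 1.4 at ICC 0.01 and 2.5 at ICC 0.05 (ICCs assumed).

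**The case against.** The case on the other side is substantial.

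- **The claim about bias is comparative.** The article says child report should be less biased, not unbiased, and a child answering with help is still less exposed than a teacher rating the child. This stands. A reader might infer that Table 1 contradicts the rationale; it does not, it only weakens it.
- **The mechanism is conjecture.** Nothing described in the pack concerns questionnaire choice, teachers may simply judge reading level in both arms alike, and staff support applies to both forms. This also stands: the text shows that measurement can differ by arm, not that it will.
- **The study is a mainly descriptive feasibility study.** No efficacy decision rests on the score, and the illustrative bias is below the standard error for all children at an ICC of 0.01 or more. This lowers the severity. It does not remove the point, because the stated aim includes testing the proposed trial methods, and the bias would carry into a larger trial where the standard error is smaller.
- **A fuller protocol may settle whether the form carries forward.** That is possible. But the article does more than stay silent: it states open discretion, and the route through staff help exists whichever form is used.
- **Locking the form has a price.** With about a year between assessments, every child aged 7 at baseline would be at least 8 at follow-up, and any of them on the 5–7 form would stay on it under a strict lock. This stands and shapes the fix.

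**Conclusion.** The concern holds as a weakness of the measurement procedure. A stated rule lets people who know the allocation influence the form and the help behind the planned primary outcome, and blinding the analyst does not address it.

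The magnitude is not established. The 0.25–1.0 point bias and the 0.26–2.1 point signal rest on an assumed switching difference, form difference and benefit, and the share affected runs from about 5% to 42% depending on which of the article's figures is used. A reader might infer that the bias is as large as any plausible effect. The document does not support that: at 42% affected, the assumed bias is at most about half the assumed signal, and it reaches or exceeds the signal only towards the 5% end. The direction is also unknown.

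This should be fixed, but it does not invalidate a feasibility study whose analyses are mainly descriptive.

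**What to change.** Replace open discretion with a form assignment set before randomisation. This can be the teacher's baseline decision or a pre-stated age or reading rule, and it must say what happens when a child turns 8. The study team, which already supplies child forms carrying individual study IDs, then issues the follow-up form under that rule. This removes the form-choice part of the bias by construction.

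It does not remove differential help. For that, give staff a short standard script for support, and record for each child the form used and any adult help. Report form switches and help by arm, and add a sensitivity analysis in children who completed the same form both times.

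The cost is some extra sorting of forms and a tick-box. Under a strict lock, some children who have turned 8 would also remain on the younger form.

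If follow-up is already complete, report the form used by arm, run the same-form sensitivity analysis, and write the assignment rule into the full trial.

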## Methods and analysis

### Design

The design of this feasibility cRCT is shown in the flowchart in figure 1. The processes for children referred to the eye clinic as part of the intervention are shown in figure 2.

**Figure 1 F1:**
[figure not shown]
The CVI project feasibility trial flowchart. CVI, cerebral visual impairment; GP, general practitioner; REDCap, Research Electronic Data Capture; SDQ, Strengths and Difficulties Questionnaire; SENCO, special educational needs and disability coordinator.

**Figure 2 F2:**
[figure not shown]
The process of referral to the eye clinic for intervention schools. CVI, cerebral visual impairment; GP, general practitioner, ID, identification.

### Setting

The study will involve primary schools in three areas of England, UK: Gloucestershire, Somerset and Southampton. These areas were chosen because the local paediatric ophthalmologists have agreed to participate in the study. The study will be led by the study team in Bristol, UK.

### Inclusion criteria

All mainstream state-funded primary schools including academies, local authority-maintained schools and free schools, within 1 hour of travel time to the local ophthalmology unit, in the three study areas will be eligible for inclusion.

### Exclusion criteria

Schools who share a special educational needs and disability coordinator (SENCo or SENDCo), where contamination between intervention to control schools might occur, unless they are part of a linked group of schools who all participate in the trial (and will be in the same arm).

### Enrolment of schools

All schools in the study areas that meet the inclusion criteria will be sent an invitation letter and copies of the school and parent/carer information sheets. Invitation letters and information sheets will be sent out by post and email to heads, SENCos and heads of governors. The letters and information sheets will explain the study and that schools will be reimbursed for the teachers’ time completing outcome assessments.

### Legal basis for conducting the study

The legal basis for the study will be the University of Bristol undertaking a public task, as described in articles 6.1e and 9.2j of the European Union General Data Protection Regulation (EU-GDPR). It will not be on the basis of parental consent.

The head teacher will agree to participate on behalf of the children and staff in their school and will sign a Memorandum of Understanding to this effect with clear descriptions of the expectations and obligations of the study team and the participating school. This will be non-binding and is written to foster mutual understanding of what is involved—there will be no steps taken if schools are unwilling or unable to carry out all their activities. A link to the full privacy notice online will be provided to all parents and school staff and a summary of the privacy notice is included in the parent/carer information sheet (PIS) and the school information sheet.

Any parent in a participating school will be able to withdraw their child’s data from the study. This can be achieved by contacting the study team using details included in the PIS, or by completing a non-agreement to data use form that will all be sent with a PIS, plus a freepost envelope. They will be able to do this at any time up to the end of the study. In addition, if a child does not assent to filling in the child-report questionnaires, they do not have to. They will still be included in the study unless their parent has withdrawn them.

